# Two randomized controlled clinical trials to study the effectiveness of prednisolone treatment in preventing and restoring clinical nerve function loss in leprosy: the TENLEP study protocols

**DOI:** 10.1186/1471-2377-12-159

**Published:** 2012-12-18

**Keywords:** Leprosy, Prednisolone, Nerve function impairment, Subclinical neuropathy

## Abstract

**Background:**

Nerve damage in leprosy often causes disabilities and deformities. Prednisolone is used to treat nerve function impairment (NFI). However, optimal dose and duration of prednisolone treatment has not been established yet. Besides treating existing NFI it would be desirable to prevent NFI. Studies show that before NFI is clinically detectable, nerves often show subclinical damage. Within the ‘Treatment of Early Neuropathy in LEProsy’ (TENLEP) study two double blind randomized controlled trials (RCT) will be carried out: a trial to establish whether prednisolone treatment of 32 weeks duration is more effective than 20 weeks in restoring nerve function in leprosy patients with clinical NFI (Clinical trial) and a trial to determine whether prednisolone treatment of early sub-clinical NFI can prevent clinical NFI (Subclinical trial).

**Methods:**

Two RCTs with a follow up of 18 months will be conducted in six centers in Asia. In the Clinical trial leprosy patients with recent (< 6 months) clinical NFI, as determined by Monofilament Test and Voluntary Muscle Test, are included. The primary outcomes are the proportion of patients with restored or improved nerve function. In the Subclinical trial leprosy patients with subclinical neuropathy, as determined by Nerve Conduction Studies (NCS) and/or Warm Detection Threshold (WDT), and without any clinical signs of NFI are randomly allocated to a placebo group or treatment group receiving 20 weeks prednisolone. The primary outcome is the proportion of patients developing clinical NFI. Reliability and normative studies are carried out before the start of the trial.

**Discussion:**

This study is the first RCT testing a prednisolone regimen with a duration longer than 24 weeks. Also it is the first RCT assessing the effect of prednisolone in the prevention of clinical NFI in patients with established subclinical neuropathy. The TENLEP study will add to the current understanding of neuropathy due to leprosy and provide insight in the effectiveness of prednisolone on the prevention and recovery of NFI in leprosy patients. In this paper we present the research protocols for both Clinical and Subclinical trials and discuss the possible findings and implications.

**Trial registration:**

Netherlands Trial Register: NTR2300

Clinical Trial Registry India: CTRI/2011/09/002022

## Background

Damage to peripheral nerves is the main consequence of leprosy and may cause deformities and disabilities in patients. Nerve damage can occur before, during and after multidrug therapy (MDT) and is a result of inflammation in the nerves due to immunological reactions [1]. For many years corticosteroids, mostly prednisolone, have been used to treat nerve function impairment (NFI) in leprosy patients [2]. However, an optimal dose and duration of steroid treatment has yet to be established [3]. In addition, research should focus also on possibilities of timely detection and treatment of early (subclinical) neuropathy in order to prevent NFI and its consequences [4]. The TENLEP study is designed to obtain additional information about prednisolone treatment for preventing and restoring nerve function in people affected by leprosy. Within the TENLEP study two randomized clinical trials will be conducted; one trial focusing on patients with subclinical neuropathy, and the second trial focusing on patients with clinical NFI.

Between 6 and 27% of the 228 474 newly detected leprosy cases in 2010 [5] presented with visible impairment (grade 2 disability) [2,4]. This WHO leprosy disability grading system is the most widely used method to assess impairment in leprosy patients and is generally used for monitoring program quality [6,7]. More accurate assessments for NFI are Voluntary Muscle Testing (VMT) and Monofilament Testing (MFT) or ball point tests [8], which are widely used in clinical practice to assess motor and sensory NFI, respectively. Recently, more sensitive methods have been introduced to detect early, subclinical neuropathy. The INFIR study found that nerve conduction studies (NCS) and Warm Detection Threshold (WDT) are the most effective methods for finding subclinical nerve damage [1]. With these tests subclinical neuropathy can be detected at least 3 months before VMT and MFT can determine the first clinical impairments. Sub-clinical changes during and following MDT were also found to be predictive of new onset NFI [9].

To examine treatment of clinical NFI several studies have been conducted using prednisolone. In one cohort the WHO recommended prednisolone regimen (starting with 40 mg prednisolone/day, tapered down over 12 weeks [2]) was found not to be successful in the prevention and reversal of NFI in multibacillary (MB) patients treated for reactions or neuropathy [10]. Also a 16-week prednisolone regimen, usual practice nowadays, was found not to be very effective in two randomized controlled trials (RCT) [11,12]. One trial was in patients with Type 1 Reactions and/or NFI, receiving either prednisolone or prednisolone with intravenous methylprednisolone. Close to 50% of the patients required additional prednisolone during or after the treatment period [11]. The second RCT in MB patients with mild sensory impairment did not show a difference in NFI as measured with MFT 12 months after start of prednisolone treatment [12]. Van Veen et al. [3], reviewing RCTs comparing placebo to prednisolone treatment, conclude that studies so far have not provided enough evidence to draw robust conclusions about the long-term effect of corticosteroids on reactions and NFI. However, there is reason to assume that longer steroid treatment might be more beneficial, since one study showed that a 5 month corticosteroid regimen was significantly more effective than a 3 month regimen [13]. In TENLEP we aim to assess whether prednisolone treatment of 32 weeks duration is more effective than treatment of 20 weeks duration in restoring nerve function in patients with clinical sensory and/or motor NFI of recent onset (<6 mo), as detected by VMT and/or MFT.

The effect of prednisolone treatment on patients with subclinical neuropathy to prevent clinical NFI as determined with MFT and/or VMT has not been studied in a RCT before. The objective of the Subclinical trial is therefore to determine whether prednisolone treatment of early subclinical neuropathy, as detected with WDT and NCS, would prevent clinical sensory and/or motor function loss in leprosy patients. This paper presents the protocols for both the Clinical and the Subclinical trial.

## Methods

### Definitions

#### General

##### Neuropathy (peripheral)

Functional impairment and/or structural damage to autonomic, sensory, and motor nerve fibers within the peripheral nervous system.

##### Nerve function impairment

Sensory, motor or autonomic neuropathy evidenced by clinically detectable reduction in function in sensory, motor and/or autonomic fibers. The ‘level’ of impairment that is clinically detectable depends on the sensitivity of the testing instruments used. (It does not include abnormality of nerve conduction that is detectable only by electrophysiological means and WDT).

##### Nerve damage

An imprecise but common term for ‘neuropathy’, which is also used in relation to trauma. Here it indicates clinical or subclinical damage to a nerve, whether reversible or irreversible.

##### Neuritis

A condition in which inflammatory cells are found in the nerve, detectable by swelling and/or functional impairment with spontaneous nerve pain and/or nerve tenderness on palpation.

##### Subclinical neuropathy

Patients have normal values for Voluntary Muscle Testing and Monofilament Testing, but are impaired on Nerve Conduction Studies (NCS) and/or Warm Detection Threshold (WDT).

### Entry criteria Clinical trial

At least one nerve with either a VMT score of 4 or less on the 0–5 (modified) MRC scale or with an monofilament threshold increased compared to normal subjects by three or more monofilament levels on any test-site, two levels on one test-site AND at least one level on another test-site, OR one level on three or more test-sites for one nerve. With VMT each nerve is tested with one specific test assessing the strength of a muscle (group) innervated by that nerve. For MFT each nerve is tested on three sites).

### Entry criteria Subclinical trial

Any one parameter (Motor Nerve Conduction, Sensory Nerve Conduction, Warm Detection Threshold) abnormal in at least two nerves or any two parameters abnormal in at least one nerve. VMT and MFT values are normal.

### Outcome criteria Clinical trial

#### Restored nerve function

Monofilament Test and/or Voluntary Muscle Test of a nerve are recovered to normal levels (MFT = 0, VMT = 5).

#### Improved nerve function

At least one nerve shows better results on Monofilament Test and/or Voluntary Muscle Test. The MF thresholds should be *reduced* by three or more monofilament levels on any site, two levels on one site AND at least one level on another site, OR one level on three or more sites for one nerve. VMT score should be *increased* by at least 1 point.

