#### Clinical nerve function tests

After intake, eligible subjects will be assessed for clinical sensory and motor nerve impairment. The clinical sensory function is tested with monofilaments using a standard set of 5 Semmes-Weinstein monofilaments ranging from blue (200 mg) to pink (300 g) [22]. This test of touch sensibility is based on indenting the skin surface with a series of standard nylon filaments. For each thickness it is recorded whether or not the patient feels the touch, starting with the thinnest filament. For hands the normal threshold is the blue filament and for feet the purple (2 mg) filament; when these filaments are felt by the patient it results in a score of 0. The score increases with 1 for each thicker filament not felt, with a maximum score of 5 in hands and 4 in feet (filament of 300 g not felt) for every site. Each nerve will be tested on 3 sites. The trigeminal nerve is tested by assessing the blink regularity. A patient is diagnosed as having sensory impairment if the monofilament threshold is increased by three or more monofilament levels in one single nerve (over 3 sites).

Motor nerve impairment will be assessed with Voluntary Muscle Testing (VMT) using the 0–5 MRC scale [23,24]. The test is performed by checking the ability of the patient to move a body part to a given position and to hold that position against resistance applied by the tester. A nerve scoring lower than 5 is considered impaired. When a single score of 4 is found this score should be independently confirmed by a second assessor.

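### The monofilament improvement rule ignores rises at a nerve's other sites, so a nerve whose three-site total is unchanged or higher can count as improved (minor)

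*Protocol article*

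**What the plan says.** Under Outcome criteria Clinical trial, Improved nerve function, the article opens with "At least one nerve shows better results on Monofilament Test and/or Voluntary Muscle Test". It then gives the size of monofilament change required. The first two qualifying patterns of fall are "by three or more monofilament levels on any site, two levels on one site AND at least one level on another site". The third is a one-level fall at each of the nerve's three sites. For muscle testing a gain of one point suffices.

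These are the site patterns of the Entry criteria Clinical trial, where the comparison is with normal: "an monofilament threshold increased compared to normal subjects by three or more monofilament levels on any test-site", followed by the same two alternatives. Clinical nerve function tests restates impairment as a total, namely that "the monofilament threshold is increased by three or more monofilament levels in one single nerve (over 3 sites"). The same section says "Each nerve will be tested on 3 sites" and scores each site from 0 upward, "with a maximum score of 5 in hands and 4 in feet (filament of 300 g not felt) for every site".

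Under Outcome measures, the Clinical trial's primary outcome is the proportion of patients with restored and improved nerve function at 18 months. No section sets rises at one site against falls at another.

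**The concern.** The site patterns were built to measure loss against normal, where no site can score below 0. For change from an abnormal intake, sites can move either way. A rule that reads only the falls can then be satisfied by a nerve that has lost as much as it gained, or more. Such a nerve would count towards the primary outcome. The fault sits inside a single nerve, so it remains whether a patient succeeds on any one nerve or only on all of them, a point that the article leaves unclear.

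**Working it through.** **Inputs.** Three sites per nerve, scored 0 to 5 in hands and 0 to 4 in feet (Clinical nerve function tests); the three fall patterns (Improved nerve function); the intake requirement of sensory impairment (Entry criteria Clinical trial); 60% versus 70% recovery, one-sided 5%, 80% power, 20% loss and 720 patients (Sample size calculation). Equal allocation is assumed. The reading SDs in step 4 are also assumptions.

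**1. The plan's own figure.** The usual two-proportion formula with 60% and 70% gives 281 per arm. Allowing for 20% loss, 281/0.8 = 351.25, so 352 per arm and 704 in total. The stated 720 is 2.3% above this. The figure uses only the assumed percentages, so nothing below changes it.

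**2. Against normal, the patterns are sound.** For every one of the 6 × 6 × 6 = 216 hand states and 5 × 5 × 5 = 125 foot states, the three patterns hold exactly when the three-site sum is at least 3. This agrees with the total given in Clinical nerve function tests.

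**3. Against intake, the equivalence fails.** Examples for one hand nerve:

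| Intake | Follow-up | Pattern met | Total |
|---|---|---|---|
| (3,0,0) | (0,3,0) | fall of 3 at one site | 3 to 3 |
| (4,1,1) | (1,4,4) | fall of 3 at one site | 6 to 9 |
| (2,1,0) | (0,0,5) | falls of 2 and 1 | 3 to 5 |

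Taking every intake state with a sum of at least 3 against every follow-up state gives:

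| | Hand | Foot |
|---|---|---|
| Transitions meeting the rule | 23,913 | 6,805 |
| Total unchanged | 2,040 | 588 |
| Total higher | 3,228 | 597 |
| Net fall of 1 or 2 | 5,610 | 1,875 |
| Net fall of 3 or more | 13,035 | 3,745 |

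No net fall: (2,040 + 3,228)/23,913 = 22.0% in hands and (588 + 597)/6,805 = 17.4% in feet. These are shares of possible score pairs, all weighted equally. They are not shares of patients. The third pattern uses all three sites, so it never hides a rise; the fault is confined to the first two.

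**4. How often scatter alone would produce it.** Model: reading = true level plus normal error, rounded and limited to 0–5; intake sum at least 3; no true change. The share of hand nerves called improved with no net fall is about 0% at SD 0.5, 0.07% at SD 0.7 and 0.7% at SD 1.0.

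**5. Two possible repairs.**
- *Require a lower sum in addition to the patterns.* This removes exactly the no-net-fall cases: 5,268 hand and 1,185 foot transitions. The other 18,645 and 5,620 stay. Hardly any truly improving nerves are lost.
- *Require a net fall of at least 3 instead.* Every such fall already meets the written patterns, so this rule is strictly narrower. At SD 0.7 it lowers false improvement from 8.4% to 6.2%, which is 2.2 points. It also lowers detection of partial improvers: from 78% to 73% where half the loss recovers (5 points), and from 66% to 59% where each site falls by 0 to 3 levels (7 points).

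**The case against.** The case for leaving the rule alone has four parts.

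- *The lead-in already asks for better results.* A nerve going from 6 to 9 does not fit that description. But the sentences that follow say in numbers what better means, and a programmer would apply those.
- *Site-level recovery is a legitimate target, and the total over three sites describes impairment, not improvement.* This stands. The improvement rule contradicts no other section, and a site-based responder definition is a fair choice. It does not require counting a nerve that is no better overall.
- *The headline cases are rare under scatter, and testers were trained and checked for reliability.* This stands too, and it is why the point is minor.
- *Such detail may sit in the full protocol.* That is possible, but the article states a complete numeric rule, and that rule admits these cases.

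A reader might go further and infer that the rule materially dilutes the 60% versus 70% contrast, and that a net fall of 3 should replace it. The documents do not support this. They give no test-retest data, and most of the gap between the two rules under scatter is nerves with a net fall of 1 or 2, which read as somewhat better. On the assumed model at SD 0.7 with one nerve, a 10-point contrast becomes 10 × (1 − 0.084) = 9.16 points under the written rule and 10 × (1 − 0.062) = 9.38 under the net rule. That 0.22-point gain ignores the detection lost among true improvers, so higher power has not been shown.

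Nor should one argue that a nerve would be classed as both improved and worsened: the Clinical trial's outcome criteria contain no worsening rule.

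**Conclusion.** The point holds in a limited form. As written, the first two monofilament patterns can score a nerve as improved when its three-site total is unchanged or higher, and this feeds the Clinical trial's primary outcome. That follows from the wording and the score range alone.

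The size in patients is unknown. The 22.0% and 17.4% must not be read as error rates. The scatter figures of about 0% to 0.7% rest on assumed SDs, independent errors and true levels spread over the scale. The frequency would be higher only if sites of one nerve truly moved in opposite directions. Nothing here shows a bias between the arms or an effect on the planned 720. Severity is minor.

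**What to change.** Keep the three patterns and add one condition to the monofilament part of Improved nerve function: *and the sum of the three site scores of that nerve is lower than at intake*. The muscle-test criterion is unaffected. A nerve such as (2,1,3) to (0,0,5), with a net fall of 1, still counts.

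The cost is one clause and one line of derivation, with no new data, visits or sample size, and almost no loss of sensitivity. It should be settled before the treatment code is broken. A net fall of at least 3 levels may be added as a sensitivity analysis, with a note that it is expected to miss more partial improvers.

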#### Improved Reaction Severity Scale score

When the score on the Reaction Severity Scale [14]*decreases* by at least 3 points on the sum score or at least 2 points on any individual item in the scale.

#### Count of nerve function impairments (CNFI)

The sum of MFT and VMT scores (5 being normal) for all nerves tested in the study.

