### Outcome measures

#### The Clinical trial

The primary study outcome is the proportion of patients with restored and improved nerve function (of all nerves) measured by VMT/MFT at 18 months. Secondary outcomes are based on results of the Reaction Severity Scale, SALSA and Participation Scale (Figure 2). Furthermore, a Count of Nerve Function Impairment (CNFI) will be computed to measure the results of treatment on nerve function, with special interest for most commonly affected nerves. The CNFI will consist of the count of nerve function impairments detected by monofilament and VMT testing and will be validated in this trial.

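### The CNFI is defined as a sum of two scores that run in opposite directions, which conflicts with the protocol's own scoring rules and with its other description of the CNFI as a count of impairments

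*Protocol article*

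**What the plan says.** The protocol article describes the CNFI twice.

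- **Outcome criteria Clinical trial, Count of nerve function impairments (CNFI):** "The sum of MFT and VMT scores (5 being normal) for all nerves tested in the study".
- **Outcome measures, The Clinical trial:** "The CNFI will consist of the count of nerve function impairments detected by monofilament and VMT testing and will be validated in this trial". The same paragraph says that it is meant to measure the effect of treatment on nerve function. It is introduced after the Reaction Severity Scale, SALSA and Participation Scale outcomes.

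The scoring rules for the two components are stated separately.

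- **MFT (Clinical nerve function tests):** a site where the normal filament is felt scores 0. "The score increases with 1 for each thicker filament not felt, with a maximum score of 5 in hands and 4 in feet". On sites: "Each nerve will be tested on 3 sites".
- **VMT (same section):** a 0 to 5 scale. "A nerve scoring lower than 5 is considered impaired".
- **Restored nerve function** gives the normal values as MFT 0 and VMT 5.
- **Improved nerve function** requires a fall in monofilament levels or a rise in the VMT score.

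No section reverses or rescales either score before they are added.

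**The concern.** A total score needs one direction. Here a patient whose sensation recovers moves down and a patient whose strength recovers moves up. The offset can arise within a patient who has both kinds of impairment. It can also arise across patients within an arm, because the Clinical trial admits patients with sensory impairment, motor impairment or both.

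Two things are at stake. If the sum is computed as written, a regimen that improves both functions shows a diluted or absent difference, or one whose sign depends on which function improved more. And with two different quantities under one name, the protocol does not fix which one is analysed and validated, so the choice could be made after the data are seen.

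**Working it through.** The protocol gives no range, total or power for the CNFI, so there is no stated figure to reproduce. The check applies the stated scoring rules.

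**Inputs.** From Table 1 in Subclinical nerve function tests:
- MFT by filament on ulnar, median and radial (hand) and on posterior tibial and sural (foot).
- VMT on facial, ulnar, median, radial, common peroneal and posterior tibial.
- Both sides of the body are tested.

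From Clinical nerve function tests: 3 MFT sites per nerve, a maximum of 5 per hand site and 4 per foot site.

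Two assumptions are needed because the text is silent: the three site scores are summed, and the trigeminal blink test is left out.

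**Ranges.**
- MFT, hands: 3 nerves × 2 sides × 3 sites × 5 = 90
- MFT, feet: 2 × 2 × 3 × 4 = 48
- MFT total: 0 (normal) to 90 + 48 = 138 (worst)
- VMT total: 6 × 2 × 5 = 60 (normal) down to 0 (worst)

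**The sum as literally defined, MFT + VMT.**

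| Patient | MFT | VMT | Sum |
|---|---|---|---|
| Fully normal | 0 | 60 | 60 |
| Total motor loss, sensation intact | 0 | 0 | 0 |
| Complete sensory loss in one foot nerve (3 × 4 = 12) and 12 VMT grades lost | 12 | 48 | 60 |
| Total loss of both | 138 | 0 | 138 |
| Total sensory loss, strength intact | 138 | 60 | 198 |

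Impaired patients lie below, at and above the healthy value.

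**Dependence on the site assumption.** With one MFT score per nerve (for example the site mean), the MFT maximum is 3 × 2 × 5 + 2 × 2 × 4 = 46. Total loss of both then scores 46, below the healthy 60, whereas with summed sites it scores 138, above it. An unstated convention thus decides on which side of normal the worst patient falls.

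**Change scores for one site and one muscle.** The literal change is −(sensory gain) + (motor gain). With both components aligned it would be the sum of the two gains.

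| Sensory gain | Motor gain | Literal change | Aligned gain |
|---|---|---|---|
| 3 | 0 | −3 | 3 |
| 3 | 1 | −2 | 4 |
| 3 | 3 | 0 | 6 |
| 2 | 3 | +1 | 5 |
| 0 | 2 | +2 | 2 |

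Every row is a pure improvement, yet the literal change is negative, zero or positive.

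**The other reading of the parenthesis.** Suppose 5 is meant as normal for both tests.
- This contradicts MFT 0 as normal. On the scale as scored, 5 is the worst hand value and cannot occur on a foot site.
- Reversing the foot scale on its own maximum (4 − MFT) makes normal 4, not 5.
- Using 5 − MFT makes normal 5, but the worst foot value is then 5 − 4 = 1 rather than 0.

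Either conversion is possible, but the text states neither.

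**The same recovery under one-directional definitions.** Take MFT 3 at one site and VMT 2, recovering to MFT 0 and VMT 5.
- Literal sum: 5 to 5.
- MFT + (5 − VMT): 3 + 3 = 6 to 0.
- Count of impairments: 2 to 0, since three levels at one site meets the protocol's sensory rule and VMT 2 is impaired.

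**The case against.** The strongest reply is that the protocol already contains a sound definition. Outcome measures says "The CNFI will consist of the count of nerve function impairments detected by monofilament and VMT testing", and the measure's name is itself a count. A count has one direction and cannot cancel, so the line in the outcome criteria may be no more than a loose summary. This stands in part: it shows which definition to keep. It does not settle the conflict, because the formal outcome criterion states a different quantity.

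Second, the parenthesis is ambiguous. If it covers only VMT, the protocol does not call 5 normal for MFT. If it covers both tests, a reversed MFT is implied and nothing cancels. This also stands: the cancellation and the objection to 5 as a normal MFT value belong to different readings and cannot both apply. Each reading still leaves a defect, however: opposite directions under the first, and a contradiction with the stated MFT scoring under the second.

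Third, a reader might infer that the CNFI cannot measure a treatment effect at all. The documents do not support that. Cancellation is complete only when the sensory and motor changes are equal in size. Purely sensory or purely motor change still moves the sum. The example with 12 points gained and 12 lost was constructed to show that a tie with normal is possible, and says nothing about how often it would occur.

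Fourth, derivation detail is commonly left to a full protocol or analysis plan. That would excuse a missing rule. This is a stated rule that conflicts with other stated rules in the same article.

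**Conclusion.** The definition is wrong as written and should be corrected. Followed literally, it adds scores with opposite directions, so sensory and motor changes in the same clinical direction offset fully or partly, and the sign of a difference between arms is not reliably interpretable. Read the other way, it contradicts the MFT scoring. Under both readings it differs from the count described under Outcome measures.

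The figures 60, 138 and 198 assume summed site scores and no blink test. The opposite directions depend on neither assumption, only on the stated normal values and directions.

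Severity is moderate. It would be tempting to infer that the trial's main result is at risk, but it is not. The primary outcome is restored and improved nerve function, whose criteria state the direction correctly for each test. The sample size rests on recovery proportions and does not use the CNFI. The CNFI is a non-primary measure still to be validated, and monthly MFT and VMT data allow either version to be derived later.

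**What to change.** Use one definition of the CNFI, with the same wording in the outcome criteria and under Outcome measures, and both components in the same direction.

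- **Preferred: the count.** For each nerve and side, score 1 if MFT meets the rule under Clinical sensory impairment and 1 if VMT is 4 or less, then add. State that the MFT increase is measured against the normal threshold, as in Entry criteria Clinical trial. Zero is normal and higher is worse. From Table 1, without the blink test, the range is 0 to (5 × 2) + (6 × 2) = 22.
- **If a severity sum is wanted:** MFT score + (5 − VMT), added over nerves and sides, again with 0 as normal and higher as worse. With summed sites the range is 0 to 138 + 60 = 198, so the sensory part carries more than twice the range of the motor part. That weighting should be a deliberate choice.

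In either case, state how the trigeminal blink test enters. For the severity sum, also state how the three MFT sites are combined.

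The cost is one definition line and one derivation step, settled before unblinded data are seen. No new data, visits or change in sample size are needed.
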